#### Longitudinal qualitative data collection

Participants in the ACET group will be invited to attend a one-to-one semistructured interview at completion of the intervention (A3) to discuss their views on the intervention received and the impact of the intervention on their recovery. The discussion will cover the study protocol, effects of the intervention on their health in the short term and the feasibility of administering the intervention in a hospital setting. The findings of the analysis of the four open questions will be used to probe further during the interviews.

In-person focus groups will also be performed with staff (clinicians, occupational therapists and physical therapists) involved in clinical care/rehabilitation of patients at RJAH on study completion to ascertain the acceptability of the intervention, trial design and outcome measures, as well as the staff’s experiences during the trial. Prior to taking part in the focus group, RJAH staff will complete a screening survey, requesting descriptive characteristics such as age, sex, qualifications, job role and level of experience. A trained moderator will run the interviews/focus groups and data will be audio recorded via a secure password protected digital recording device. These interviews/focus groups will address the aforementioned themes via a semistructured interview schedule.^127^ The recorded discussions will subsequently be transcribed verbatim and analysed employing the same framework analysis protocol used in the analysis of the open-ended questions as an initial coding frame.^126^

### Data management and confidentiality

Consent forms are not anonymised and will, therefore, be kept in a secured and locked place at the clinical research facility with access only to the research team. Questionnaire responses and results sheets will be stored as paper (A1 – A3) or electronic copies (A4). Access to participant data will be granted to the research team only. Hard copies of these documents will be secured in a locked cabinet within clinical research facilities at the MCSI. All protocol contributors named in this document will have access to the final trial dataset.

Electronic data will be anonymised and stored on a password-protected university computer. A laboratory laptop computer (owned by the University of Birmingham) will only be used to conduct non-identifiable analysis of results. The data from blood samples (for analysis of CVD risk biomarkers) will be analysed by the research team in the School of Sport, Exercise and Rehabilitation Sciences. All samples will be stored with the participant code and time point, with a sample inventory created to allow for easy sample location at a given time. Deidentified study data, coded with a unique study ID assigned to each participant, will be kept at the University of Birmingham. The study-specific folder can only be accessed by the research team. Hard copies of trial data will be transported and stored in a locked cupboard at the University of Birmingham. Study data will be kept for 10 years in line with the University of Birmingham research data policy. Participants’ samples will be stored in accordance with the Human Tissue Act, 2004. Any spare stored samples may be used in the future by either the research team or their collaborators to further explore the changes in cardiometabolic health following SCI and how this might be mitigated with aerobic exercise in the subacute setting. This is only applicable to participants who have provided specific consent for this. Where this is the case, further ethical approval will be sought for additional analyses based on the General Data Protection Regulation (GDPR). Specifically, a Data Use Agreement will be established to ensure the purpose of data use, scope of data access, data security measures and any data sharing restrictions. Anonymised data will be made accessible in a public repository on request while adhering to GDPR requirements, such as providing privacy notices.

### Statistical analysis

The Shapiro-Wilk test will be used to test the distribution of the continuous variables for demographic and outcome measures. Continuous variables will be reported as mean±SD for normally distributed data or median with IQRs for non-normally distributed data; categorical variables will be reported as frequency. Specific injury characteristics will be considered for subanalysis (ie, injury level, injury severity). A two-way repeated measures analysis of variance (ANOVA) will be applied to examine the main effects of the group/time and group–time interaction. Post hoc analyses will be conducted where significant group-time interaction effects are identified. Significance level will be set at 0.05 for all statistical tests. Standardised effect sizes (Cohen *d*) will also be calculated and interpreted based on the following criteria: small (*d*=0.2), medium (*d*=0.5) and large (*d*=0.8) effects.^128^

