### Trial objectives

We aim to determine whether the addition of ACET to standard of care treatment during inpatient rehabilitation within the subacute period following SCI has beneficial effects over the current standard of care (control group, CON) rehabilitation on arterial stiffness (measured via cfPWV) and secondary health outcomes: (1) blood biomarkers related to CVD, (2) cardiac structure and function, (3) extracranial vasculature, (4) HRQOL, (5) cognitive function, (6) physical activity level, (7) cardiorespiratory fitness, (8) motor function and (9) feasibility outcomes in individuals with subacute SCI. In comparison to CON, we hypothesise that the physical and metabolic stimuli of ACET will maintain cfPWV at a level that is comparable to normative age-matched values reported in the general population.^63^

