### Eligibility criteria

#### Randomisation

After preintervention assessments (A1 and A2), recruited participants will be randomly allocated into one of the two study groups using a computer-generated randomiser. Figure 1 provides an overview of the trial flow, illustrating the sequence of assessments, randomisation and subsequent testing. The A1 and A2 assessments are conducted prior to randomisation to gather initial data on participants to understand initial status and variability among participants. Conducting randomisation after these assessments minimises the risk of allocation bias, which could occur if knowledge of group assignment influenced initial measurements. Randomisation will be performed by an independent researcher ([name]) not involved in the recruitment process to minimise selection bias. Block randomisation methods will be used to ensure balance in group sizes. In consultation with the Director of Statistics and Research Strategy at the Birmingham Clinical Trials Unit, it was determined that any imbalances of the participants recruited to the study would be down to chance. Each participant will be assigned a unique participant identification number and the corresponding trial group will be provided according to the list. Blinding is not achievable during data collection, therefore, neither participants nor data collectors will be blinded. However, to minimise bias, data analysts will be blinded to participant allocation.

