**Figure 3 F3:**
[figure not shown]
Study flow chart. Following participant identification and initial assessments (**A1**) at MCSI, assessments will be repeated after a period of standard care (which will primarily involve bed rest depending on the severity of injury) (**A2**). Participants thereby act as their own controls. At this point, participants will be randomised to receive either standard of care inpatient rehabilitation (CONTROL) or standard of care inpatient rehabilitation plus 30 min of ACET, 3–5 times per week (ACET INTERVENTION) for 10 weeks, with postassessments (**A3**). 6 months after discharge (~36 weeks) into the community, follow-up HRQOL assessments will be carried out (**A4**). ABPM, ambulatory blood pressure monitoring; ACET, arm-crank exercise training; HRQOL; health-related quality of life; SCI, spinal cord injury.

The A1 assessment serves as a time point for characterising key outcome measures on admission into inpatient rehabilitation, providing a baseline of cardiovascular health. Given the significant adjustments participants face following this life-changing injury, we have streamlined some of the secondary outcome measure assessments between A1 and A2 to minimise participant burden. Therefore, rehabilitation physical activity energy expenditure, 24-hour BP monitoring and motor function assessments will be conducted only once between A1 and A2, as outlined in table 2. The rationale for having both A1 and A2 assessments for the cardiovascular measures and HRQOL questionnaires is twofold: (1) to gauge any variability or changes in responses between the time close to admission (A1) and the adjustment to their new injury (A2; for example, following initial standard of care therapy sessions) and (2) to establish multiple baselines for these outcome measures, thereby allowing participants to serve as their own controls and capturing the inherent variability in these outcomes.

**Table 2 T2:** Schedule of enrolment, interventions and assessments

Study procedures	Screen	Baseline(A1)	A1–A2	Preintervention/randomisation(A2)	Training sessions	Final week	Postintervention(A3)	Community follow-up(A4)*
Visit (V)	V1	V2	V2/V3	V3/V4	V4/V5–V45/V46	V46/V47	V47/V48	V48/V49
Eligibility								
Informed consent	X							
Medical history/demographics	X							
Changes in medication/health status				X			X	
Pregnancy screening	X							
International Standards for Neurological Classification	X						X	

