### Power calculation and sample size

We aim to recruit 42 participants for this study. This sample size was based on the effect size drawn from the CHOICES multicentre RCT.^129^ Our a priori power calculation indicated that a sample size of 32 individuals with SCI, 16 in each group, is sufficient to detect a between-group interaction effect for cfPWV, using a two-way repeated measures ANOVA with 95% power and a 5% level of significance to detect exercise group differences of ≥1 m/s. Our target effect size of 1 m/s aligns with reported exercise intervention effects in high-risk populations and represents a clinically meaningful improvement, as each 1 m/s increase in cfPWV corresponds to a 15% increased risk of cardiovascular mortality.^130 131^ A recent study found that ~16% of participants who were randomly assigned to a 5-week ACET intervention in the subacute setting discontinued the intervention.^132^ To account for the longer intervention duration in this trial, a more conservative (30%) dropout rate was estimated. Hence, 42 participants in total will be enrolled in the study.

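### The group-by-time repeated-measures ANOVA gives pre-randomisation visits the role of outcome times; a baseline-adjusted comparison at A3 would be more focused and more powerful, using data already collected

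*Protocol article*

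**What the plan says.** The Statistical analysis section fixes the method: "A two-way repeated measures analysis of variance (ANOVA) will be applied to examine the main effects of the group/time and group–time interaction". On follow-up tests it adds "Post hoc analyses will be conducted where significant group-time interaction effects are identified". On the level for every test it says "Significance level will be set at 0.05 for all statistical tests". It does not say which visits form the time factor, and it names no baseline covariate.

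The Power calculation and sample size section rests on the interaction: "a sample size of 32 individuals with SCI, 16 in each group, is sufficient to detect a between-group interaction effect for cfPWV". The method, power and level behind that figure are then given as "using a two-way repeated measures ANOVA with 95% power and a 5% level of significance to detect exercise group differences of ≥1 m/s".

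Two other places fix what the visits are. The Randomisation section states "After preintervention assessments (A1 and A2), recruited participants will be randomly allocated into one of the two study groups". The Assessments section gives as one purpose of the repeated early measurement to "establish multiple baselines for these outcome measures, thereby allowing participants to serve as their own controls". Table 2 marks cfPWV at A1, A2 and A3. A4 is questionnaires only.

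**The concern.** A3 is the only cfPWV value that treatment can affect, so at least one level of the time factor must be a pre-randomisation visit. Three consequences follow.

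- **Group main effect.** It averages A3 with visits at which the true difference is zero. It is listed among the tested effects at 0.05 but does not estimate the treatment effect.
- **Interaction over three visits** (the natural reading of Table 2). It asks whether the two groups' profiles differ in any way. One of its two degrees of freedom is the A1-to-A2 change, which happens before anyone is allocated. The A3 contrast is reached post hoc, after a significant interaction.
- **Interaction over A2 and A3 only.** It has one degree of freedom and is the difference in change from A2. It isolates the treatment effect, but it sets A1 aside and is less efficient than adjusting for baseline.

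At stake are power in a trial planned on 32 evaluable participants, and a primary result that is not tied in advance to one randomised contrast in m/s.

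**Working it through.** **Inputs from the protocol article.** Difference 1 m/s; 5% level; 95% power; 16 per group (Power calculation and sample size). cfPWV at A1, A2, A3 (Table 2).

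**Inputs assumed.** The article gives neither the SD (σ) of cfPWV nor its within-person correlation (ρ), so the stated 32 cannot be reproduced. I take ρ = 0.5, 0.7, 0.8 with equal correlations between visits, and an effect at A3 only. I solve for the SD at which the stated size gives 95% power. For the three-visit interaction this SD is 0.81, 1.05 and 1.28 m/s; for A2–A3 only it is 0.76, 0.98 and 1.20 m/s.

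**Step 1, group main effect.** The expected difference is (0 + 0 + 1)/3 = 0.33 m/s over three visits, or (0 + 1)/2 = 0.5 m/s over two. With n per group and δ the A3 effect, the noncentrality over three visits is (n/2)(δ/3)² / [σ²(1+2ρ)/3]. At ρ = 0.7, σ = 1.046: (8 × 0.1111) / (1.094 × 2.4/3) = 0.889/0.875 = 1.02, a power of about 16%. At ρ = 0.5 and 0.8 it is 28% and 12%.

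**Step 2, three-visit interaction.** Noncentrality is nδ² / [3σ²(1−ρ)] on (2, 60) df. At ρ = 0.7: 16 / (3 × 1.094 × 0.3) = 16.2, giving the planned 95.0%. The 1-df contrast of A3 against the mean of A1 and A2 has the same noncentrality but gives 97.4%, so the extra degree of freedom costs about 2.4 points.

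**Step 3, A2–A3 interaction.** Noncentrality is nδ² / [4σ²(1−ρ)] on (1, 30) df. At ρ = 0.7, σ = 1.046: 16 / (4 × 1.094 × 0.3) = 12.2, or 92.2%. ANCOVA on A2 reduces the variance by the factor σ²(1−ρ²) / [2σ²(1−ρ)] = (1+ρ)/2, which is 0.75 to 0.90 for ρ 0.5 to 0.8.

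**Step 4, ANCOVA at A3 using both baselines.** With equal correlations the residual variance is σ²[1 − 2ρ²/(1+ρ)]. At ρ = 0.7: 1.094 × (1 − 0.98/1.7) = 0.463, noncentrality 8/0.463 = 17.3 and power 98.0% with the A1/A2 mean as covariate. Entering A1 and A2 separately costs one more error degree of freedom and gives about 97% by simulation.

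**Step 5, when correlation decays by visit.** The A1–A2 interval is flexible and may include prolonged bed rest (Assessments), so equal correlations are doubtful. I keep the same SDs and simulate with correlation r between adjacent visits and r² between A1 and A3.

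| Power at 16 per group, % | Equal correlations, 0.5 / 0.7 / 0.8 | Decaying, 0.5 / 0.7 / 0.8 |
|---|---|---|
| Three-visit interaction | 95 / 95 / 95 | 90 / 88 / 86 |
| A2–A3 interaction (change score) | 92 / 92 / 92 | 92 / 92 / 92 |
| ANCOVA, A1/A2 mean | 98.5 / 98.0 / 97.8 | 96 / 92 / 90 |
| ANCOVA, A1 and A2 separately | 98 / 97 / 97 | 96 / 94 / 93 |

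ANCOVA on A2 alone has 97.3 / 95.5 / 94.5 under equal correlations, so it does not beat the three-visit interaction at 0.8. Under decay at 0.7–0.8 it has 94–95%. Separate covariates hold up under both structures; the mean does not.

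**Step 6, larger SD.** At 1.5 m/s with equal correlations of 0.5–0.8, the three-visit interaction has 46–86% and ANCOVA on the A1/A2 mean 61–92%, a gap of 15 to 6 points.

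**The case against.** The planned test is conventional and valid. Randomisation makes the expected A1 and A2 differences zero, and simulated type I error is close to 5% for every test considered. If time means A2 and A3, the interaction is exactly the difference in change. The trial is powered on the interaction, so the low power of the group main effect is not the power of the trial. The gain at the planned 95% is a few points and rests on an SD and correlation that the article does not give. All of this stands, and it limits the point to power and focus.

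Four stronger readings are tempting, and the documents do not support them.

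- *The interaction produces spurious exercise effects.* Under no effect (correlation 0.7, 40,000 simulations), 48% of significant three-visit interactions come with a non-significant contrast of A3 against baseline. But that is 2.4 points of a correct 5%, and the planned post hoc analyses would show it. Only 1.6% of null trials had a significant interaction with A3 differing significantly neither from the baseline mean nor from A2.
- *No planned test isolates the treatment effect.* This fails if only A2 and A3 enter, and the article does not name the time levels.
- *Participants missing a visit are discarded.* The article sets no missing-data rule; that can be left to the full analysis plan.
- *The hypothesis is untested.* Trial objectives does say that ACET "will maintain cfPWV at a level that is comparable to normative age-matched values reported in the general population", but that sentence opens with a comparison against CON, and the stated aim is benefit over standard of care. The interaction addresses that between-group question.

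**Conclusion.** The point holds as a correctable weakness in a stated method. On any reading of the time factor, the group main effect is diluted and is not a treatment effect. On the three-visit reading, the primary test spends one of two degrees of freedom on a pre-randomisation change and reaches the A3 contrast only after passing a significance gate. On the two-visit reading, the effect is isolated but with less precision than baseline adjustment allows.

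With the SD set for 95% power at 16 per group, adjusting for both baselines gains about 2 to 4 points under equal correlations (about 97–99% against 95%). If correlation decays by visit (0.5–0.8), the gain is about 6 to 7 points (92–96% against 86–90%). It may be more if the SD is larger than the stated size implies. These sizes depend on the assumed SD and correlations. The dilution of the main effect and the composition of the 2-df test do not.

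**What to change.** State in Statistical analysis that the single primary analysis is the ACET minus CON difference in cfPWV at A3, in m/s with a 95% CI, from ANCOVA with A2 and A1 entered as separate covariates. An equivalent choice is a mixed model with group means constrained equal at A1 and A2 and an unstructured covariance. Report this estimate regardless of any interaction test, and do not interpret the group main effect as a treatment effect. If the repeated-measures ANOVA is kept as a supporting analysis, name its time levels. Label the comparison with normative values in Trial objectives as descriptive.

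The cost is one or two error degrees of freedom (28 or 29 instead of the 30 of the change-score test) and a change of wording. No new data, visits or participants are needed. The change should be made before any unblinded analysis.

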### Power calculation and sample size

We aim to recruit 42 participants for this study. This sample size was based on the effect size drawn from the CHOICES multicentre RCT.^129^ Our a priori power calculation indicated that a sample size of 32 individuals with SCI, 16 in each group, is sufficient to detect a between-group interaction effect for cfPWV, using a two-way repeated measures ANOVA with 95% power and a 5% level of significance to detect exercise group differences of ≥1 m/s. Our target effect size of 1 m/s aligns with reported exercise intervention effects in high-risk populations and represents a clinically meaningful improvement, as each 1 m/s increase in cfPWV corresponds to a 15% increased risk of cardiovascular mortality.^130 131^ A recent study found that ~16% of participants who were randomly assigned to a 5-week ACET intervention in the subacute setting discontinued the intervention.^132^ To account for the longer intervention duration in this trial, a more conservative (30%) dropout rate was estimated. Hence, 42 participants in total will be enrolled in the study.

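### The enrolment target of 42 does not leave the 32 completers needed for 95% power at the plan's own 30% dropout rate

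*Protocol article*

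**What the plan says.** All the figures stand in one paragraph of the protocol article, Power calculation and sample size.

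- Required number: "a sample size of 32 individuals with SCI, 16 in each group, is sufficient to detect a between-group interaction effect for cfPWV", "with 95% power and a 5% level of significance", the target being "to detect exercise group differences of ≥1 m/s".
- Dropout: about 16% discontinuation is cited from a 5-week arm-crank trial in the subacute setting. Because this intervention lasts longer, "a more conservative (30%) dropout rate was estimated".
- Result: "Hence, 42 participants in total will be enrolled in the study".

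The result is presented as following directly from the dropout allowance, and no other reason for 42 is given. The Abstract repeats 42 as the trial size. The Statistical analysis section sets the test level: "Significance level will be set at 0.05 for all statistical tests".

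**The concern.** A dropout allowance should leave the required number of participants after the expected loss. The required number is therefore divided by the proportion retained. Multiplying it by one plus the dropout rate gives a smaller figure, and the gap grows with the rate. At 30% the two methods differ by four participants here, and the stated total agrees with the multiplication.

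What is at stake is the power claim for the primary outcome. If the trial loses the 30% it plans for, it will have fewer evaluable participants than the number to which the 95% is attached. This is not a detail left to a fuller document: the required number, the dropout rate and the enrolment target are all stated, and they are incompatible.

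**Working it through.** **Inputs, all from Power calculation and sample size unless noted:** 32 evaluable participants (16 per group); power 95%; level 0.05 (also in Statistical analysis; sidedness is not stated, two-sided assumed); dropout 30%; enrolment 42. No SD, standardised effect or within-person correlation is given, so the 32 itself cannot be reproduced.

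**1. Reproducing the stated 42**
- n × (1 + dropout): 32 × 1.30 = 41.6, rounded up to 42. Per group: 16 × 1.30 = 20.8, rounded up to 21, or 42 in total. This matches.
- n / (1 − dropout): 32 / 0.70 = 45.7, rounded up to 46. Per group: 16 / 0.70 = 22.9, rounded up to 23, or 46 in total. This does not match, and rounding cannot explain a gap of 4.

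That the first formula was used is inferred from the match.

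**2. What 42 delivers at 30% dropout**
- Expected completers: 42 × 0.70 = 29.4, against 32 required.
- With 46: 46 × 0.70 = 32.2.
- Largest dropout at which 42 still leaves 32: (42 − 32) / 42 = 10 / 42 = 23.8%.

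This step holds however 42 was obtained.

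**3. Effect on power, as a guide only**

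Model (assumed): two-sample t test on the change in cfPWV, two-sided 0.05, df = n₁ + n₂ − 2, noncentrality d × √(n₁n₂ / (n₁ + n₂)). The effect d is solved back from the article's own sample size. If 16 per group gives exactly 95%, d = 1.318. If 16 is only the smallest group size that reaches 95%, d can be anything from 1.318 up to just below 1.364, the value at which 15 per group would already reach 95%.

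| Completers | Power at d = 1.318 | Power at d = 1.364 |
|---|---|---|
| 16 + 16 | 95.0% | above 95% |
| 15 + 15 | 93.6% | 95.0% |
| 15 + 14 | 92.7% | 94.3% |
| 14 + 14 | 91.8% | 93.5% |

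For the 28 or 29 completers to be expected, power is about 92–94%.

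**4. Chance of reaching 32 completers**

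If each participant is lost independently with probability 0.30, the binomial probability of at least 32 completers is about 24% with 42 enrolled and about 60% with 46.

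**The case against.** The strongest reply is that the consequence is small. Power stays above 90% in every row of the table. At the cited dropout of about 16%, 42 would leave 42 × 0.84 = 35.3 completers, more than required. The design, endpoint and analysis are untouched. This stands, and it limits the importance of the point. It does not remove the inconsistency, because the plan chose 30%, not 16%.

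Second, the power figures come from a simpler model than the planned repeated measures ANOVA, with inputs the article does not give. This also stands: they are a range under stated assumptions, and no single value from them belongs in the protocol.

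Third, loss need not be equal between groups. The cited 16% is discontinuation among people assigned to exercise, and the withdrawal rule for missed sessions can apply only to that arm. If only that arm lost 30%, 21 × 0.70 = 14.7, about 15, would remain beside 21 controls, 36 in all. But the article applies its 30% to the total, so this is a different scenario and does not support the stated figure.

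A reader might infer two further faults that the article does not support.

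- One is that 30% is not really cautious, since 16% over 5 weeks at a constant rate gives 1 − 0.84² = 29.4% over 10 weeks. The article compares 30% with the cited 16% and gives the longer duration as its reason. On that comparison the description is correct, and the extrapolation, which itself assumes a constant rate, if anything supports 30%.
- The other is that the 42 are counted at consent, so that losses before randomisation come on top. No passage says so. The Randomisation section states: "After preintervention assessments (A1 and A2), recruited participants will be randomly allocated", which fits 42 randomised equally well, and no loss rate between A1 and A2 is given.

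**Conclusion.** Wrong as written, of minor to moderate importance. The required 32, the 30% dropout and the 42 enrolled cannot all hold. At the plan's own dropout rate, 42 leaves about 29 completers. The 32 are preserved only if dropout is at most about 24%, and 46 would be needed at 30%. These statements are plain arithmetic on the article's figures and need no further assumption.

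The power consequence does rest on assumptions: a two-sample t model on change, a two-sided 0.05 test, roughly equal loss in the two groups, and 16 per group as the smallest size reaching 95%. Under these, power is about 92–94% instead of the stated 95%. It would be tempting to call the trial underpowered, but this slip alone does not show that.

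**What to change.** Reword the end of Power calculation and sample size in one of two ways, keeping 42:

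1. State that 42 participants retain the 32 completers needed for 95% power provided dropout does not exceed about 24%, and that 46 would be needed at 30%; or
2. State that 42 participants with 30% dropout give about 29 evaluable, and report the power at that number, recomputed by the authors from the SD and within-person correlation behind their own calculation. The 92–94% above is a check on the order of magnitude and should not be copied in as the result.

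The cost is a change of wording, plus one recalculation for the second option. No extra participants are needed. The price is a slightly less favourable statement: a lower dropout tolerance or a lower power than now claimed.
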